### Statistical analysis

General linear mixed models using the ‘lme4’ package in R software [56] will be used to assess the impact of treatment (L2L or control), time (treated as categorical with levels baseline, intervention end and follow-up) and the group-by-time interaction. The primary endpoint of the study will be intervention end (Term 3: weeks 5–10). Our analyses will be adjusted for the clustering of effects at the class and school levels, using random intercepts. Our mediation analyses will use a full information maximum likelihood procedure in Mplus. To determine whether changes in *peer leaders’* on-task behaviour mediate the effect of the L2L program on teachers’ work-related stress and wellbeing, structural equation models will be used to test the following: (i) the total effect of the program on work-related stress and well-being (C pathways); (ii) the effect of the intervention on the mediators (A pathways); (iii) the mediator effects on teachers’ work-related stress and well-being (B pathways); (iv) the direct effect of the L2L on teachers’ work-related stress and well-being with the inclusion of mediators in the model (Cʹ pathways) and (v) the indirect effect of L2L on teachers’ work-related stress and well-being (AB pathways).

To determine whether changes in *peers’* fundamental movement skills mediate the effect of the L2L program on their executive functioning, structural equation models will be used to test: (i) the total effect of the program on executive functioning (C pathways), (ii) the effect of the program on the mediators (A pathways), (iii) the mediator effects on executive functioning (B pathways), (iv) the direct effect of the program on executive functioning with the inclusion of mediators (C’ pathways), and (v) the indirect effect of the program on executive functioning (AB pathways). As Mplus does not support bootstrapping with clustered data, single-level bootstrap confidence intervals will be compared with confidence intervals adjusted for clustering.

Data regarding schools’ exposure to potential sources of contamination (or co-intervention) will be assessed via items in school, teacher, and Principal surveys following the intervention period. Potential effects on outcomes will be explored via sensitivity analyses.

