### Sample size calculation

To ensure 80% power to detect a conservative effect of *d* = 0.50 for leadership effectiveness (adjusted between-group difference of ∼0.4 units with standard deviation of 0.8), we required 128 *peer leaders* for a non-clustered trial (two-tailed, *p*<0.05). However, as recommended by CONSORT [27], we adjusted our power calculation for the clustering of effects at the school level using a correction factor of [1+ (m − 1) × ICC], where m = participants per school and ICC = intraclass correlation coefficient. Assuming an average class size of 20 participating students, two classes per school and an ICC for leadership effectiveness of 0.15, the correction factor is 5.68 [i.e., 1 + (40−1) × 0.15]. The required sample size to achieve 80% power with α levels set at *p* < .05 is 727 (i.e., 128 x 5.68). Operating under the assumption that each school has approximately 60 x Stage 3 students (two classes), with a conservative response rate of 67% and allowing for an expected 10% loss to follow-up, we will aim to recruit at least 40 Stage 3 students from each of 20 schools (*N* = 800). We will also recruit 40 Stage 2 students per school (*N* = 800).

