#### Primary outcome (*peer leaders*)

Completed by *school champions* at baseline (Term 1: weeks 8–10 to Term 2), and intervention end (Term 3: weeks 5–10):

*Leadership effectiveness*. *School champions* will be asked to rate *peer leaders’* leadership skills using an adapted version of the Transformational Teaching Questionnaire [40]. The questionnaire was developed to assess the tenets of transformational leadership theory: idealised influence, inspirational motivation, intellectual stimulation, and individual consideration. Using the common stem ‘*The student that I’m rating*…’, the questionnaire includes the following items: ‘behaves as someone that other students can trust’ (idealized influence), ‘is enthusiastic about what other students are capable of achieving’ (inspirational motivation), ‘encourages students to think for themselves’ (intellectual stimulation), and ‘shows that s/he cares about the students s/he is teaching’ (individualised consideration)’. The measure requires respondents to answer four questions for each student, using a five-point scale ranging from ‘0 –*not at all*’ to ‘4 –*frequently’*. The scores of each item are summed to create a composite score. This four-item composite measure of leadership effectiveness was found to have acceptable internal consistency in our pilot (α = 0.89 to 0.92) [24].

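### The group-by-time test uses class and school intercepts that are constant over time, so cluster-level change counts as student-level error and the primary standard error is right only by coincidence

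*Protocol article*

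**What the plan says.** The Statistical analysis section specifies linear mixed models in lme4 with treatment, "time (treated as categorical with levels baseline, intervention end and follow-up) and the group-by-time interaction". On clustering it says "Our analyses will be adjusted for the clustering of effects at the class and school levels, using random intercepts". It names intervention end as the primary endpoint. It mentions neither a student random effect nor any term that lets a school or class effect differ between occasions.

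Under Primary outcome (peer leaders), leadership effectiveness is scored at baseline and again at intervention end. The school champions do the scoring: "The measure requires respondents to answer four questions for each student". Table 1 identifies the champions as the teachers of the participating Stage 3 classes. So the same students are scored twice, most naturally by their own class teacher.

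The Sample size calculation section gives an SD of 0.8, an ICC of 0.15, 40 peer leaders per school, 20 schools and 10% loss to follow-up. It gives no correlation over time for a student, class or school.

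**The concern.** The group-by-time effect compares change over time between arms. A school or class intercept that takes the same value on both occasions drops out of every change score, so it adds nothing to the error of that comparison. The between-cluster error that remains is variation in change: schools that move differently over two terms, or a teacher who rates the whole class more generously the second time. The stated model has no place for it except the residual, which is averaged over several hundred students rather than over 20 schools.

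The primary p-value and confidence interval are at stake. They would not carry the right between-school error in a trial that randomises schools, and nothing in the fitted model would reveal it.

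**Working it through.** **The plan's own figures.** The article gives no standard error for the group-by-time effect, so there is none to reproduce. Its unclustered total of 128 reproduces (64 per arm, t-based). Its correction factor does not: 1 + 39 × 0.15 = 6.85, not 5.68. That is a separate matter, and neither factor is used below.

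**Inputs from the article.** SD 0.8 (variance 0.64); ICC 0.15; 20 schools; 40 × 0.9 = 36 students analysed per school.

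**Assumptions.** Equal allocation, 10 schools per arm; all of the ICC at school level at first; cluster autocorrelation C and student autocorrelation S, both varied because the article gives neither.

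**Formulas.** The common factor is (2/10) × 2 × 0.64 = 0.256.

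- True variance of the group-by-time effect: 0.256 × [0.15(1 − C) + 0.85(1 − S)/36]
- Variance reported with class and school intercepts alone: 0.256 × [0.85 + 0.15(1 − C)]/36
- Variance reported if a student intercept is added: 0.256 × [0.85(1 − S) + 0.15(1 − C)]/36
- Actual type I error at nominal 5%: 2 × [1 − Φ(1.96 × reported SE / true SE)]

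The cluster term 0.15(1 − C) is undivided in the true variance but divided by 36 in both reported variances. The SD cancels from the ratio, so the type I error does not depend on it.

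**Worked case, C = 0.8, S = 0.5.** True: 0.256 × [0.030 + 0.0118] = 0.01070, SE 0.103. Reported: 0.256 × 0.880/36 = 0.00626, SE 0.079. Ratio 0.765; 1.96 × 0.765 = 1.50; type I error 13%.

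**Results at S = 0.5.**

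| C | True SE | Reported SE, class + school | Type I | Reported SE, student intercept added | Type I |
|---|---|---|---|---|---|
| 1 | 0.055 | 0.078 | 0.6% | 0.055 | 5% |
| 0.95 | 0.070 | 0.078 | 3% | 0.055 | 12% |
| 0.9 | 0.083 | 0.078 | 6% | 0.056 | 19% |
| 0.8 | 0.103 | 0.079 | 13% | 0.057 | 28% |
| 0.7 | 0.121 | 0.080 | 19% | 0.058 | 35% |
| 0.5 | 0.149 | 0.081 | 29% | 0.060 | 43% |

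The reported SE barely moves (0.078 to 0.081) while the true SE nearly triples.

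**Where the direction changes.** Setting the first two variances equal gives 1 − C = 0.85 S/(0.15 × 35). The switch is at C = 0.95, 0.92 and 0.89 for S = 0.3, 0.5 and 0.7. At C = 0.8 the type I error over the same range of S is 16%, 13% and 11%.

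**Part of the ICC at class level.** Class-level change averages over more units, so the inflation is milder. Simulation (4,000 trials per scenario) gave 7% to 12% at C = 0.8. With the ICC split 0.08 school and 0.07 class, and S = 0.6, it gave 0.2%, 9% and 24% at C = 1, 0.8 and 0.5. With a student intercept added, the last two became 26% and 42%.

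**Comparison.** In the same simulations, school-level analyses kept close to 5%: 4.5% to 5.4% for school mean change on 18 degrees of freedom, and 4.3% to 5.0% for baseline-adjusted school means.

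**The case against.** The strongest objection is that the article is condensed. The sentence on random intercepts describes how clustering is handled; it does not say that no other random effect will be fitted. A student term may stand in the full analysis plan, and its absence here is not evidence of omission. That is correct, but it does not rescue the model. As the last two columns of the table show, a student intercept without cluster-by-time terms makes the SE too small for any C below 1.

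A reader might infer that both missing terms push the SE down, or that it is usually too small. The documents support neither. Omitting the student term alone makes this SE too large, which is why the test is conservative when C is 1. Under the structure as printed, a too-small SE needs C below about 0.89 to 0.95, and the article gives no value. One teacher rating a class twice cuts both ways: constant leniency is stable and cancels, while a change in leniency does not.

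A reader might also infer that the clustering allowed for in the sample size is wrongly lost. The stable part of a school effect should cancel from a difference in change; only the time-varying part is wrongly dropped. Nor does the article say that a z-test will be used: naming lme4 does not settle the reference distribution. Finally, preferring baseline adjustment to a difference in change on grounds of efficiency is a choice, not an error in the plan.

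**Conclusion.** The point holds as a misspecification of the primary analysis, wrong as written. A group-by-time test with time-constant class and school intercepts gives a correct standard error only where the two effects happen to offset each other, or, with a student intercept added, where cluster effects are perfectly stable.

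As printed, the error can go either way: a type I error of about 0.6% at C = 1 and S = 0.5, against 11% to 16% at C = 0.8 with all of the ICC at school level, and less if part is at class level. With a student intercept but no cluster-by-time term, it goes one way only: about 19% at C = 0.9 and 28% at C = 0.8 (S = 0.5). These sizes rest on assumed autocorrelations and equal allocation. The misspecification itself does not.

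**What to change.** State the primary analysis as a model of the intervention-end score with arm and the student's baseline score as fixed effects, random intercepts for school and for class within school, and small-sample degrees of freedom (Kenward-Roger or Satterthwaite). The school intercept then carries the between-school error at the endpoint that the arm comparison needs. Keep further school-level covariates few: 20 schools leave about 18 school-level degrees of freedom, and each covariate uses some.

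If the repeated-measures form is kept, add a student random intercept and school-by-time and class-by-time random effects, again with small-sample degrees of freedom.

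The cost is a few lines of text and code, settled before outcome data are analysed by arm. The interval will be wider where schools or raters drift. The repeated-measures form may give singular fits with this many variance components, so say in advance what will be done then.

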*Time-on*-*task in the classroom*. Classroom observations will be conducted by trained research assistants using established methods [45]. To increase standardisation across schools, where possible the observations will take place during Mathematics or English lessons at the same time of day. During each 30-minute observation period (starting 5 minutes after students enter the classroom), research assistants will assess the on-task and off-task behaviour of six randomly selected students (5 minutes per student). For each lesson, two observers will randomly select 6 boys and 6 girls (i.e., 12 students in total) and the order in which they are observed (teachers and students will not know who is being observed). The same students will be assessed at the end of the intervention. Observers will listen to an audio file via headphones, which will inform them when to observe and record (in 15 second intervals). After each interval, the observers will record the student’s behaviour by recording an appropriate code (i.e., actively engaged, passively engaged, off-task motor, off-task verbal, or off-task passive) using an observation recording sheet. Time spent on- and off-task during the lesson will be expressed as a percentage of the 30-minute classroom observation.

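### Class and school intercepts cancel from the group-by-time contrast, so the primary test's standard error carries no cluster-level change variance and holds 5% only by coincidence

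*Protocol article*

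**What the plan says.** The Statistical analysis section names `lme4` and lists the fixed effects as treatment, "time (treated as categorical with levels baseline, intervention end and follow-up) and the group-by-time interaction". It adds that "The primary endpoint of the study will be intervention end". Clustering is covered in one sentence: "Our analyses will be adjusted for the clustering of effects at the class and school levels, using random intercepts". The section mentions no pupil intercept, cluster-by-time effect, random slope or cluster-robust standard error for this model.

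The Sample size calculation does treat the school as the unit that limits precision: "we adjusted our power calculation for the clustering of effects at the school level". For the primary outcome the raters are the school champions, whom Table 1 identifies as the teachers of the Stage 3 classes. They score their pupils at baseline and again at intervention end: "The measure requires respondents to answer four questions for each student".

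**The concern.** In a cluster trial, the variation that limits a comparison of changes is how differently whole schools and classes change. A random intercept that is constant over time describes how clusters differ in level. It protects a comparison at a single time point but not a comparison of changes. The sample size therefore pays for school clustering, while the standard error of the test that decides the trial has no such component.

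A second feature works the other way. Without a pupil intercept, the stable part of each child's score stays in the residual and enlarges the standard error. The two errors offset each other by an amount that depends on quantities the protocol does not give. The p-value and interval for the primary outcome are at stake, and so are those for every student outcome analysed with the same model.

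**Working it through.** **The plan's own figure.** The unclustered total is 128, and 128 × 5.68 = 727, as stated. However, 1 + 39 × 0.15 = 6.85, which gives 128 × 6.85 = 877; the factor 5.68 corresponds to an ICC of 0.12. That is a separate inconsistency. I use 0.15 below and give a range that includes 0.12.

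**Inputs from the protocol.** 20 schools, 2 classes per school, 20 pupils per class less 10% loss = 18 analysed, ICC 0.15, two-sided 5%.

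**Assumptions.** 10 schools per arm; total variance 1; pupil autocorrelation 0.7; ICC either split as 0.05 school and 0.10 class, or all at school level; cluster persistence r (the correlation of a cluster's effect between baseline and end) varied. Pupil variance is 1 − 0.15 = 0.85.

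**True variance of the contrast**

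(2/10) × [2·σ²school·(1−r) + 2·σ²class·(1−r)/2 + 2·σ²pupil·(1−0.7)/36]

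At r = 0.8 with the split ICC: 0.2 × [0.0200 + 0.0200 + 0.0142] = 0.01083, so the true SE is 0.104.

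**Variance reported by the model as written**

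4·σ²resid/360, where 360 is the number of pupils per arm (10 × 36). There is no ICC term. The residual pools pupil variance with a diluted share of the cluster-by-time variance:

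σ²resid = {0.85 × 17 × 80 + 38 × [18 × 0.15 × (1−r) + 0.85 × 0.3]} / 1398

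Here 80 is the number of class-by-time cells, 38 = 40 classes − 2, and 1398 = 1440 − 40 − 2. At r = 0.8: (1156 + 38 × 0.795)/1398 = 0.8485, so the reported SE is √(4 × 0.8485/360) = 0.097.

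**Type I error** = 2 × Φ(−1.96 × reported SE / true SE). At r = 0.8: 1.96 × 0.0971/0.1041 = 1.83, or 6.75%.

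| Persistence r | Reported SE | True SE, split ICC | Type I | True SE, all at school | Type I |
|---|---|---|---|---|---|
| 1.0 | 0.096 | 0.053 | <0.1% | 0.053 | <0.1% |
| 0.9 | 0.097 | 0.083 | 2.2% | 0.094 | 4.4% |
| 0.8 | 0.097 | 0.104 | 6.8% | 0.122 | 11.8% |
| 0.7 | 0.098 | 0.122 | 11.7% | 0.144 | 18.5% |

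Simulation under the null agrees: with the split ICC it gives about 0.1%, 2.6%, 7% and 12% in the same order. A t-test on school-mean change with 18 df stayed close to 5% in every scenario.

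**Other inputs.** With 20 pupils per class, ICC 0.12 to 0.15 and pupil autocorrelation 0.5 to 0.7, the model as written gives 0-0.8% at r = 1, about 2-7% at 0.9, 6-15% at 0.8 and 19-31% at 0.5.

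**Where 5% is met.** For the base inputs, at r of about 0.84 (split ICC) or 0.89 (all at school level). Above that the test is conservative. At r = 1, power for a 0.2 SD effect is about 58-59%, against about 94-95% with a correct standard error.

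**If only a pupil intercept is added.** At r = 0.9 the reported SE falls to 0.055 against a true 0.083 (split) or 0.094 (all at school level). Type I error is then 19% or 25%. It is 5% only at r = 1.

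**The case against.** The strongest reply is that this is a journal article. The sentence on random intercepts does not say that no other random terms exist, and a fuller plan might hold the exact formula. That has weight for the pupil intercept, whose absence alone would not be a finding. It has less weight for the cluster structure, because the article states how clustering is handled, and that method does not protect the contrast it is paired with. A pupil intercept supplied elsewhere would not rescue the test either.

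A reader might infer that the plan simply inflates false positives. The documents do not support that. As written, the test is conservative when cluster effects persist strongly, and it is inflated only below roughly 84-90% persistence in the base scenarios. The 19-25% figures belong to a model with a pupil intercept, which the protocol does not state.

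A reader might also infer that the protocol shows teachers' ratings drifting class by class. It does not. Ratings by the class teacher at both occasions make shared change plausible, but nothing in the text demonstrates or quantifies it.

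Finally, the primary coefficient is not named. In a plain comparison of groups at intervention end the intercepts would not cancel. Group-by-time is the natural reading of the listed terms, but it is an inference.

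**Conclusion.** The point holds in this form. If the primary test is the baseline-to-end group-by-time contrast, the stated random effects leave its standard error without any school-level or class-level change variance, and the stated 5% level is met only by coincidence. The cancellation is exact for balanced data. The size and direction of the error rest on the assumed cluster persistence, pupil autocorrelation and ICC split: from about 0.1% at full persistence to 12-19% at 70%. A correct error structure removes this dependence, so the sentence should be changed before the data are analysed.

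**What to change.** **Student-level outcomes in the repeated-measures model.** State random intercepts for student, class and school, plus class-by-time and school-by-time random effects, for example `(1|student) + (1|class) + (1|class:time) + (1|school) + (1|school:time)`. Test the named contrast at intervention end with Kenward-Roger or Satterthwaite degrees of freedom (about 18 for 20 schools). For singular fits, fix in advance a t-test on school-mean change with 18 df.

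**Alternative.** Analyse intervention-end scores adjusted for baseline, with class and school intercepts and the same small-sample degrees of freedom. There the intercepts do their work, because the outcome enters at one time only.

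**Teacher stress and well-being.** These have no student level, and with one teacher per class a class-by-time term cannot be separated from the residual. Use a teacher intercept with school and school-by-time effects, or school-mean change.

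**Cost.** A few sentences and model terms, and no new data. Some intervals will widen, and five variance components on 20 schools will sometimes give singular fits. Power for d = 0.50 stays above 95% at 80% persistence or more under the base inputs. It falls to about 93% at 60% persistence with the split ICC, and to about 91% at 70% with all clustering at school level.

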## Materials and methods

### Research design

L2L will be evaluated using a two-arm parallel group cluster RCT. Schools will be randomly allocated to a group by an independent researcher via a computer-based random number generator to either an intervention or wait-list control. In Australia, the school year is divided into four terms, each approximately 10 weeks in duration. The study will be conducted across two cohorts (2022 and 2023), with assessments at baseline (between mid-March to June, Terms 1 and 2), intervention end (mid-August to September, Term 3), and follow-up (November to mid-December, Term 4). See Fig 1 for the SPIRIT Schedule Of Enrolment, Interventions, And Assessments. The trial has been prospectively registered with the Australian New Zealand Clinical Trials Registry (registration number: ACTRN12621000376842). The design, conduct and reporting will adhere to CONSORT (Consolidated Standards of Reporting Trials) [27] and TIDieR (Template for Intervention Description and Replication) [28] checklists. The trial has been approved by the University of Newcastle’s ethics committee (reference number: H-2020-0109) and the NSW Department of Education’s State Education Research Applications Process (SERAP; reference number: 2020143).

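### The single-level bootstrap interval planned for the FMS-to-executive-function indirect effect ignores school randomisation, and the valid clustered interval beside it is not given priority

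*Protocol article*

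**What the plan says.** All references are to the protocol article.

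- **Unit of randomisation** (Research design): "Schools will be randomly allocated to a group by an independent researcher".
- **Numbers** (Sample size calculation): there are 20 schools, and for the younger pupils "We will also recruit 40 Stage 2 students per school". The only ICC in the article is 0.15, for leadership effectiveness.
- **Clustering in general** (Statistical analysis): "Our analyses will be adjusted for the clustering of effects at the class and school levels, using random intercepts". This comes before the mediation text.
- **Mediation** (Statistical analysis): "Our mediation analyses will use a full information maximum likelihood procedure in Mplus". Two models follow. In one, peer leaders' on-task behaviour mediates teacher outcomes; in the other, peers' FMS mediates executive functioning.
- **Intervals**: the FMS paragraph ends with a software reason, "As Mplus does not support bootstrapping with clustered data", and then the plan that "single-level bootstrap confidence intervals will be compared with confidence intervals adjusted for clustering".

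Nothing in the section says which of the two intervals supports a conclusion about mediation.

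**The concern.** The indirect effect is the product of the A path (allocation to FMS) and the B path (FMS to executive function). Allocation varies only between schools, so what is known about the A path comes from 20 schools, not from about 800 pupils. Resampling individual pupils treats the 800 as independent and understates the standard error of A, and hence of A × B.

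A comparison with a valid interval does not repair this. With any positive ICC the single-level interval is expected to be the narrower, so where the two disagree it will usually be the one that excludes zero. An analyst could report mediation on that interval and still have followed the article. The question matters because the Introduction names mediation of executive functioning by FMS as something the trial will examine.

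**Working it through.** **Plan's own figures.** The article states no figure for the mediation intervals, so there is none to reproduce. Its only clustering figure is the sample-size correction factor of 5.68. That does not follow from its stated inputs, since 1 + 39 × 0.15 = 6.85; it is a separate matter and is not used below.

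**Inputs.**
- Peers per school, m: 40 as recruited, or 40 × 0.9 = 36 if the 10% loss in the sample size section also applies to peers.
- ICC for FMS: not given. Assumed range 0.01 to 0.15.

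**Step 1: the A path.** The design effect is DE = 1 + (m − 1) × ICC. An interval that ignores clustering has 1/√DE of the correct width. Its actual coverage is 2Φ(1.96/√DE) − 1, taking equal school sizes and a normal approximation.

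| ICC (assumed) | DE, m = 36 | √DE | Width as share of correct | Coverage, m = 36 | Coverage, m = 40 |
|---|---|---|---|---|---|
| 0.01 | 1.35 | 1.16 | 0.86 | 91% | 90% |
| 0.02 | 1.70 | 1.30 | 0.77 | 87% | 86% |
| 0.05 | 2.75 | 1.66 | 0.60 | 76% | 75% |
| 0.10 | 4.50 | 2.12 | 0.47 | 64% | 62% |
| 0.15 | 6.25 | 2.50 | 0.40 | 57% | 55% |

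Worked row: at ICC 0.05 and m = 36, DE = 1 + 35 × 0.05 = 2.75, √2.75 = 1.66 and 1.96/1.66 = 1.18, which gives 76%.

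**Step 2: the indirect effect itself.** The A × B product was simulated with 20 schools of 40, a school-level exposure, b = 0.3, the same ICC for mediator and outcome, 300 replicates and 300 bootstrap draws, using percentile intervals. Simulation error is roughly 1.5 to 3 percentage points.

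| ICC | a | Coverage, pupils resampled | Coverage, schools resampled within arm |
|---|---|---|---|
| 0.02 | 0 | 85% | 90% |
| 0.05 | 0 | 72% | 92% |
| 0.15 | 0 | 53% | 93% |
| 0.02 | 0.5 | 88% | 93% |
| 0.05 | 0.5 | 80% | 89% |
| 0.15 | 0.5 | 64% | 93% |

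With a = 0 there is no indirect effect, and the single-level interval excluded zero in 15%, 28% and 47% of replicates at the three ICCs. School resampling did so in 10%, 8% and 7%. At ICC 0 the single-level bootstrap covered 93%, so the loss comes from clustering and not from the bootstrap as such.

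A second simulation over ICC 0.02 to 0.15 gave single-level coverage of about 60 to 87% (a = 0) and 67 to 90% (a = 0.5), against 92 to 94% for cluster-adjusted intervals. The exact figures should be read as approximate; the pattern is the same.

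**The case against.** The strongest reply is that the valid interval is already planned, in the same sentence, with an honest reason for the pairing, and that the section says earlier that analyses adjust for class and school. This stands. A reader might infer that the mediation conclusions rely on single-level intervals; the article does not say so.

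A second reply is that a rule for choosing between intervals in a secondary analysis can sit in an analysis plan that is not shown. This also stands for the missing rule alone. It does not dispose of the point, because computing an interval that ignores the randomised unit, and setting it beside the valid one, is a choice the article itself makes.

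Third, the size depends on unknowns. There is no ICC for FMS or executive function. The 0.15 belongs to leadership scores given by teachers and should not be carried over to FMS scored from video by research assistants. When the A path is truly non-zero the loss of coverage for A × B is smaller than for A alone, as the a = 0.5 rows show. Both points are accepted, which is why a range is given.

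Finally, a reader might extend the point to the model asking whether "on-task behaviour mediate the effect of the L2L program on teachers" stress and well-being. With 12 pupils observed per lesson, repeating each teacher's score on pupil rows would suggest an error of √12 = 3.5-fold in the standard error. The documents do not support this. No pupil-row analysis is described, and the bootstrap sentence closes the FMS paragraph without clearly reaching the teacher model. With one row per teacher and about two teachers per school, the design effect even at an assumed ICC of 0.15 is 1 + 1 × 0.15 = 1.15, and the interval has 1/√1.15 = 93% of the correct width.

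**Conclusion.** The point holds in a limited form. One of the two intervals planned for the FMS-to-executive-function indirect effect does not respect school randomisation and will under-cover. The shortfall is modest if the FMS ICC is 0.01 to 0.02 and serious at 0.05 or above. It rests on assumed ICCs, equal school sizes and 36 to 40 analysed peers per school. The planned cluster-adjusted interval is not affected. What is wrong is that the article puts a valid and an invalid interval on the same footing, so a false claim of mediation would remain within the plan. The primary outcome and the sample size are not touched. Minor.

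**What to change.** State that inference for each indirect effect rests on one interval that respects school clustering, and name it before results are seen. The planned cluster-adjusted interval would do. Two options also allow for the skewed distribution of a product:

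- a Monte Carlo interval for A × B drawn from the cluster-adjusted Mplus estimates and their covariance matrix (preferred); or
- a bootstrap that resamples whole schools within arm, run outside Mplus. With 20 schools its percentile version covered 89 to 93% in the table above, so it falls slightly short of nominal.

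Drop the single-level bootstrap, or keep it labelled as descriptive only. The cost is a sentence or two of wording, a short script and wider intervals. Data collection does not change.
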